### Statistical Analysis

Baseline characteristics will be summarized and stratified by intervention group. The primary outcomes—adherence to dietary guidelines, KAPs, and patient satisfaction with medical care—will be compared between groups by using a log-rank test. A Cox proportional hazards regression model will be used to adjust for confounders that differ significantly between the two groups at the .20 level of significance. A generalized linear mixed model using a binomial distribution and logit link function will be used to examine the binary secondary objective—subjects’ satisfaction with medical care. The group types (ie, the intervention and control groups) will be used as a fixed effect, and subject data will be used as random effects. This will be done by using a variance components covariance structure. To adjust for confounders that differ significantly between the two groups at the .20 level of significance, covariates will be added to the model, and a linear regression model will be used.

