### Study Groups

The study participants were randomly assigned into the following two groups: the intervention group (telephone-linked dietary decision support system) and the control group (paper-based diet record; Figure 1). The randomization was conducted following the assessment of participants’ eligibility for inclusion in the study. Study participants in the intervention group (group 1) recorded their daily dietary intake by using a telephone-linked, personalized, human-centered dietary decision support system and received personalized feedback and diet education via SMS text messaging. The personalized, human-centered dietary decision support system is a telephone-linked decision support system designed to provide tailored dietary education to patients with diabetes. The study participants were able to access the personalized, human-centered dietary decision support system through their computers, cell phones, or a telephone-linked service, depending on the technology platform available to them. The telephone-linked service enabled the participants (including those who did not have a technology platform to access the personalized, human-centered dietary decision support system) to receive phone calls from our research team in order to record their daily dietary intake. The personalized, human-centered dietary decision support system also generated automatic alerts that served as reminders to the participants who had not reported their daily diet intake. Study participants in the control group were provided with a paper-based diet record for documenting their daily dietary intake. Both the intervention group and control group were provided with a diabetes educational booklet at baseline. However, the study participants in the control group were also provided with a booklet to document their diet log on a daily basis. Follow-up visits were conducted at 3 and 6 months from the baseline in both groups. Baseline data were gathered on sociodemographics; health literacy; physical activity; anthropometric measurements; blood sugar testing; and diabetes knowledge, attitudes, and practices (KAPs). Follow-up data were gathered on anthropometric measurements, diabetes KAPs, blood sugar testing, and satisfaction with medical care.

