### Outcomes

The study outcomes include dietary KAPs. These outcomes were assessed by using the following tools. Satisfaction with medical care was also assessed.

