### Sample Size Justification

The sample size calculation was based on knowledge, attitude, and behavior outcomes, as reported in previous studies [22]. To detect a mean change of 0.2 with an SD of 0.7 at a 2-sided .05 α level of significance and a power of 85%, a sample size of 200 individuals in each group is needed. The total participant sample size will be 800.

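### Primary outcomes are defined inconsistently: up to five variables are primary, with no main outcome or visit and no stated error control, while the sample size rests on one two-sided .05 test

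*Protocol article*

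**What the plan says.** - **Statistical Analysis** gives the primary outcomes as "adherence to dietary guidelines, KAPs, and patient satisfaction with medical care", to be "compared between groups by using a log-rank test". Further on, the same section describes a mixed model for the "binary secondary objective—subjects’ satisfaction with medical care". Satisfaction is thus both primary and secondary.
- **Outcomes** opens with "The study outcomes include dietary KAPs" and adds that satisfaction was assessed too. Adherence is not mentioned there, and the subsections that follow describe no measure of it. They do describe separate knowledge, attitude and behavior scales, each with its own scoring, and no composite.
- **Sample Size Justification** rests on knowledge, attitude and behavior together: "To detect a mean change of 0.2 with an SD of 0.7", "at a 2-sided .05 α level of significance". It names no scale and no visit.
- **Study Groups** states: "Follow-up visits were conducted at 3 and 6 months from the baseline in both groups". Neither visit is named as the main one.
- The article states no success rule and no adjustment for several outcomes.

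**The concern.** A trial sized on one two-sided .05 test supports a claim at that level only if the outcome and time point carrying the claim are fixed in advance. Here they are not, and the sections that should fix them disagree. If some outcomes differ between arms and others do not, the article gives no way to tell whether the trial succeeded.

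This matters in practice because the abstract's conclusions and the Discussion anticipate better results on KAPs, satisfaction and overall diabetes management. With several findings expected and no ranking among them, a report could put the favorable ones first, and the nominal 5% would no longer describe the risk of a false finding.

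**Working it through.** **Inputs.** From Sample Size Justification: difference 0.2, SD 0.7, two-sided .05, power 85%, 200 per group, 800 in total. From Results: 400 per arm (200 urban and 200 rural in each). Correlations between outcomes are not given, so a range is assumed.

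**Step 1: the plan's own figure.** The usual formula for two means is n = 2 × [SD × (z₀.₉₇₅ + z₀.₈₅) / difference]² = 2 × [0.7 × (1.960 + 1.036) / 0.2]², which gives 220 per group against 200 stated. At 200 per group, power is 81.5%. This is a separate matter. At 400 per arm power is 98.1%, so the overall comparison is not short of participants. No familywise error rate is stated that could be reproduced.

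**Step 2: counting the primary outcomes.**

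| Section | Outcomes implied as primary | Number |
|---|---|---|
| Sample Size Justification | knowledge, attitude, behavior | 3 |
| Outcomes | the three KAP scales, with satisfaction assessed in addition | 3 (or 4) |
| Statistical Analysis, satisfaction read as secondary | adherence and the three KAP scales | 4 |
| Statistical Analysis, list of primary outcomes | adherence, the three KAP scales, satisfaction | 5 |

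**Step 3: error rates if every outcome is tested at two-sided .05 and any one significant result counts.** For k independent tests, the chance of at least one false difference in either direction is 1 − 0.95ᵏ. The chance of at least one false result in favor of the intervention is 1 − 0.975ᵏ. Correlated cases come from multivariate normal simulation with no true effect (300,000 to 500,000 draws).

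| Tests | Assumed correlation | Either direction | Favoring intervention |
|---|---|---|---|
| 1 | – | 5.0% | 2.5% |
| 4 | 0 | 18.5% | 9.6% |
| 4 | 0.5 | 15.6% | 7.7% |
| 5 | 0 | 22.6% | 11.9% |
| 5 | 0.5 | 18.3% | 9.2% |
| 5 | 0.7 | 14.8% | 7.4% |
| 10 (five outcomes, two visits) | 0 | 40.1% | 22.4% |
| 10 | 0.5 between outcomes, 0.5 between visits | 31.2% | 15.8% |
| 10 | 0.7 and 0.7 | 23.5% | 11.7% |

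**Step 4: power with three primary scores under Holm.** The strictest step uses .05/3 = .0167 (z = 2.394). Power is Φ(difference / [SD × √(2/n)] − z).

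- 400 per arm: 0.2 / (0.7 × √(2/400)) = 4.041. At .05, 4.041 − 1.960 = 2.081, power 98.1%. At .0167, 4.041 − 2.394 = 1.647, power 95.0%.
- 320 per arm (assumed 20% loss): 0.2 / (0.7 × √(2/320)) = 3.614. At .0167, 3.614 − 2.394 = 1.220, power 88.9%.

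These powers are for a difference in means, as in the sample size section, and apply the same 0.2 and 0.7 to all three scales.

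**The case against.** The strongest reply is that a condensed article may leave the multiplicity procedure, the success rule and the analysis visit to a full protocol or analysis plan that is not shown. That stands for the bare absence of an adjustment. It does not cover what the article itself fixes. The article declares a set of primary outcomes, gives one of them a second and opposite status, and does not list another among the study outcomes. A later plan could not settle this without overriding the published text.

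The reply is also right about several stronger readings that a reader might infer:

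- **That the chance of a false claim of benefit is 18-40% instead of 5%.** Those figures are rates for a difference in either direction. In the intervention's favor, the corresponding range is about 9-22%, and the single-test reference is 2.5%.
- **That the plan tests each outcome at both visits.** It does not say so. A log-rank test as written gives one test per outcome over follow-up. The 40% figure needs ten separate tests that are also independent, which repeat measurements on the same people would not be.
- **That every outcome is tested at .05 and any one suffices.** The .05 level appears only in the sample size paragraph, and no success rule is stated. The text does not exclude such a rule either.
- **That the Outcomes section recognizes KAPs alone.** It also mentions satisfaction; only adherence is missing.

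Holm on the KAP scores is one valid strategy among several. The reason to prefer it is that it follows the outcomes the sponsor listed and sized the trial on.

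**Conclusion.** The concern holds as a defect in how the primary outcomes are fixed. Their number is three, four or five depending on the section, no outcome or visit leads, and the sample size supports one two-sided .05 test.

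Assuming two-sided .05 for each outcome and success on any one:

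- Five outcomes: about 15-23% for a false difference in either direction (correlation 0.7 to independent).
- Four outcomes, with satisfaction secondary: about 16-19% (correlation 0.5 to independent).
- Five outcomes, false result favoring the intervention: about 9-12% (correlation 0.5 to independent), against 2.5% for one test.

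Separate testing at both visits would raise the two-sided rate further, to 40% if all ten tests were independent. These are conditional illustrations, since the article states neither the testing rule nor the correlations. The inconsistency between sections depends on none of them.

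**What to change.** Reconcile Outcomes, Sample Size Justification and Statistical Analysis so that they name the same primary set:

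- Make the knowledge, attitude and behavior scores the primary family at one named visit, for example month 6.
- Test them with Holm at overall two-sided .05 on the 400 versus 400 comparison.
- Make adherence, satisfaction and the other visit secondary, and remove the double label on satisfaction.

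Set this before outcome data by arm are examined. The article describes follow-up as ongoing and expected to finish by October 2019, but was published in March 2022, so the documents do not show whether that is still possible. If it is not, report the hierarchy as a post hoc change.

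The cost is wording plus a small loss of power: for a 0.2/0.7 difference in means, from about 98% to about 95% at the strictest Holm step, or about 89% with an assumed 20% loss to follow-up. No additional participants are needed.

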### Study Enrollment and Data Collection Procedure

Data were collected at baseline, and follow-ups were conducted at months 3 and 6, resulting in 4 data collection time points. After each time point, the field-workers scheduled follow-up interviews to administer the study questionnaires. The study staff who were collecting data were blinded to the group assignments.

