#### Nutrition Knowledge Scale

The Nutrition Knowledge Scale comprises the following four types of items: (1) 10 items on the relationship between diet and disease, (2) 10 items on food comparisons in terms of their nutrient content (eg, fat, fiber, calcium, calories, and sodium); (3) 6 items on the daily serving requirements of different food groups; and (4) 5 items on weight and weight loss. The scale is in a multiple-choice format, and 1 point is awarded for correct answers; otherwise, 0 points are awarded. The interitem reliability (Cronbach α coefficient) of the Nutrition Knowledge Scale is .78 [20].

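### The log-rank test and Cox model do not apply to the KAP and satisfaction scores as defined, and do not estimate the mean difference the trial was sized for

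*Protocol article*

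**What the plan says.** The Statistical Analysis section names the primary outcomes as "adherence to dietary guidelines, KAPs, and patient satisfaction with medical care" and states that they "will be compared between groups by using a log-rank test". It continues: "A Cox proportional hazards regression model will be used to adjust for confounders that differ significantly between the two groups", using a .20 significance level to choose them. The same paragraph then returns to satisfaction: "A generalized linear mixed model using a binomial distribution and logit link function will be used to examine the binary secondary objective", with subject as a random effect. It ends by adding covariates and a linear regression model.

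The Outcomes subsections describe scores:
- **Knowledge:** 10 + 10 + 6 + 5 = 31 items, where "1 point is awarded for correct answers; otherwise, 0 points are awarded".
- **Attitude:** 8 + 6 + 5 = 19 items on a 5-point Likert scale.
- **Behavior:** 15 + 9 = 24 items, each scored 1 to 5.
- **Satisfaction (CSQ-8):** 8 items on a 4-point Likert scale.

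On timing, the enrollment section says: "Data were collected at baseline, and follow-ups were conducted at months 3 and 6". Study Groups lists KAPs at baseline and follow-up, and satisfaction at follow-up only. The Data Analysis Plan intends to check continuous outcomes for normality and transform them if needed. The Sample Size Justification reads: "To detect a mean change of 0.2 with an SD of 0.7".

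**The concern.** A log-rank test compares the times at which participants reach an event, and a Cox model estimates a ratio of hazards for that event. Each needs an event, a time to it and a rule for censoring. A KAP or CSQ-8 score at month 3 or month 6 supplies none of these, and the article does not say how a score would become an event.

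Two things are at stake. First, whoever runs the analysis has to improvise, either by treating the score as if it were a time or by choosing a cut-off that counts as the event. Nothing in the article governs that choice, and it would have to be made for knowledge, attitude, behavior and satisfaction separately. If it is made after the data are seen, the primary result depends on it. Second, the resulting hazard ratio has no clear meaning for a questionnaire score and does not estimate the mean change on which the sample size rests. Some power is also lost, though this matters less.

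**Working it through.** **1. Outcome type against method.** The article treats the outcomes in three ways that do not fit together:
- The outcome definitions and the normality checks treat them as scores, summarised by means.
- The sample size uses a mean change and an SD. It gives no hazard ratio, event count or event rate.
- The primary analysis uses log-rank and Cox.

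The first two agree and the third stands apart. Satisfaction is in conflict a second time: it is listed as primary under the log-rank test, then called a binary secondary objective under a binomial mixed model.

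**2. The plan's own sample size.** For a two-sided .05 test and 85% power:

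n per group = 2 × [SD × (z₀.₉₇₅ + z₀.₈₅) / δ]² = 2 × [0.7 × (1.960 + 1.036) / 0.2]² ≈ 220.

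The article states 200, which does not reproduce. That is a separate matter. What counts here is that the calculation is for a difference in means, whereas a log-rank calculation cannot be attempted from the stated inputs. The total of 800 is enrolled as 400 per arm, with 200 per arm in each of the urban and rural settings.

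**3. Cost in power if log-rank is forced onto the scores.** Assume normal scores, a shift of 0.2, SD 0.7 and no loss to follow-up. The noncentrality is 0.2 / (0.7 × √(2/n)):
- n = 400 per arm: 4.041
- n = 200 per arm: 2.857

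The noncentrality is multiplied by the square root of each method's efficiency relative to comparing means:
- Score used as time: ∫ φ²/(1 − Φ) = 0.903, so efficiency is 0.903² ≈ 0.82.
- Score cut at the median: √(2/π) = 0.798, so efficiency is 2/π ≈ 0.64.

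Power = Φ(noncentrality × factor − 1.96):

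| Method | 400 per arm | 200 per arm (one setting) |
|---|---|---|
| Compare means | Φ(2.081) = 98.1% | Φ(0.897) = 81.5% |
| Score as time | Φ(1.689) = 95.4% | Φ(0.621) = 73.3% |
| Median split | Φ(1.264) = 89.7% | Φ(0.320) = 62.5% |

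The t distribution gives 81.3% for means at 200 per arm.

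The article gives no dropout rate. Assuming 10% loss (360 per arm), the three figures for the overall comparison are 97.0%, 93.4% and 86.4%. Assuming 20% (320 per arm), they are 95.1%, 90.4% and 82.2%.

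**4. A version built on the visits.** Suppose the event were the first visit at which the score passes a threshold, so that only months 3 and 6 are possible event times. A simulation of 2,000 trials assumed a control mean of 0, SD 0.7, a shift of 0.2 at both visits, within-subject correlation 0.5, and a threshold of 0.35 or 0.7:
- At 400 per arm, log-rank power was about 96% and 91%, against about 98% to 99% for a t-test of month 6 scores.
- At 200 per arm, it was about 71% and 65%, against about 80% to 82%.
- With no true difference, the log-rank test rejected in 3.9% to 5.8% of trials, close to the nominal 5%.

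**The case against.** The article condenses a fuller document, and event and censoring definitions could sit in an analysis plan that is not shown. Their absence alone therefore carries no weight. This does not dispose of the point, because the article does state a test and does define the KAP and CSQ-8 outcomes, and the two do not fit. An analysis plan could apply log-rank to these scores only by creating a different endpoint.

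Several stronger readings are tempting, and the documents do not support them:
- **That the analysis is invalid in the sense of false positives.** A threshold version can be computed, and in the simulation its type I error stayed near 5%. The accurate statement is that the methods do not apply to the outcomes as defined.
- **That every primary outcome is a questionnaire score.** Adherence to dietary guidelines is listed as primary without an instrument or definition. Diet is recorded daily in both arms, so a time-to-event form is conceivable, although none is given.
- **That the trial loses its power.** The falls to 73% and 63% belong to 200 per arm. The overall comparison has 400 per arm, where even the median split stays above the 85% target if follow-up is complete. It drops below the target, to 82.2%, under an assumed 20% loss.
- **That baseline scores are discarded.** Baseline KAPs are collected and could enter as confounders under the .20 rule. The plan does not ensure that they will.
- **That pairing within a participant is ignored throughout.** The binomial model for satisfaction has a subject random effect.

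**Conclusion.** The point stands for the KAP and satisfaction outcomes. The named primary test and adjustment model do not fit the outcomes as the article defines them, and their result would not be the mean difference for which the trial was sized. The main consequence is a primary analysis without a clear meaning and with an open, possibly data-driven, choice of event. A larger sample does not cure that.

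The loss of power is modest for the overall comparison: from about 98% to about 95% or 90%, under normal scores, the plan's 0.2 and 0.7, and complete follow-up. It is material only within one setting, from about 81% to about 73% or 63%. For adherence no judgement on the method is possible until the outcome is defined.

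**What to change.** - **KAP scores:** replace log-rank and Cox with a comparison of means on the month 3 and month 6 scores, adjusted for baseline score and urban or rural setting. A linear mixed model or ANCOVA would serve. State which visit is primary, as the article does not, and report the adjusted mean difference with its 95% CI.
- **Satisfaction:** state once whether it is primary or secondary, and whether it is continuous or binary. If continuous, analyse the CSQ-8 total by the same model without a baseline term, because it is listed at follow-up only. If binary, keep the binomial mixed model and define the cut-off.
- **Adherence to dietary guidelines:** define it and give it an analysis that matches. Keep log-rank and Cox only if it is defined as a time to an event.

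The cost is wording in the protocol and analysis plan. The analyses use data the trial already plans to collect; the article describes month 3 and 6 follow-up as ongoing. No larger sample is needed for the overall comparison: comparing means at 400 per arm has 98.1% power, or 95.1% with an assumed 20% loss.

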### Study Design

A quasi-experimental trial was conducted between the period of June and December 2018 (Figure 1). Study participants were recruited from the following two urban and rural locations: Community Health Center, Dharamshala, Kangra (urban population), and Model Rural Health Unit, Haroli Block, Una (rural population). Eligible study participants included (1) adults aged ≥30 years, (2) those with controlled or uncontrolled diabetes, (3) those who agreed to participate in the study, (4) those who were available for follow-up interviews, and (5) those with a telephone or computer at home. Diabetic status was based on a physician-confirmed diagnosis of diabetes and the prescription of medications for diabetes management. The exclusion criteria comprised the following: (1) the presence of any mental or physical challenge affecting the study participants’ ability to use an electronic diet record, (2) unavailability for a telephone follow-up, and (3) involvement in other clinical trials or protocols related to dietary assessments. The study was funded by the Indian Council of Medical Research.

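### Covariates are selected by baseline tests at the .20 level although assignment is described as random, so the adjusted models would usually omit a baseline KAP score and can never include setting

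*Protocol article*

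**What the plan says.** All references are to the protocol article. Statistical Analysis gives the selection rule twice.

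- For the primary outcomes, a Cox model is meant to "adjust for confounders that differ significantly between the two groups at the .20 level of significance".
- After the mixed model for satisfaction: "To adjust for confounders that differ significantly between the two groups at the .20 level of significance, covariates will be added to the model", followed by mention of a linear regression model.

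No covariate is named as entering regardless of that test. The unadjusted primary comparison is a different one: "The primary outcomes—adherence to dietary guidelines, KAPs, and patient satisfaction with medical care—will be compared between groups by using a log-rank test".

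On allocation, Study Groups states: "The study participants were randomly assigned into the following two groups". Study Design says: "A quasi-experimental trial was conducted between the period of June and December 2018". The Abstract uses both descriptions.

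Study Groups lists the KAP measures among the baseline data, and Outcomes and Statistical Analysis treat KAPs as study outcomes. Results reports 400 per group, made up of 200 control and 200 intervention participants in each of the urban and rural settings.

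**The concern.** If assignment was random, any baseline difference between the groups is chance. A significance test then says nothing about which variables are worth adjusting for. What makes a covariate useful is its association with the outcome, and the screen ignores that. Baseline KAP, probably the strongest predictor of follow-up KAP, enters only when chance has unbalanced it. Setting, by which the groups are reported as stratified and for which the Discussion expects differences, does not enter at all.

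At stake are the precision of the adjusted estimates and the accuracy of their stated error rates. The final model also depends on the baseline data rather than on a choice made in advance.

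**Working it through.** **Inputs.** Difference 0.2, SD 0.7, two-sided α .05, power 85% and 200 per group come from Sample Size Justification. The 400 per arm, 200 per arm in each setting, comes from Results. The .20 threshold comes from Statistical Analysis. The baseline/follow-up correlation ρ is not given; 0.3, 0.5 and 0.7 are assumed.

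**1. The plan's own figure.** n = 2(z₀.₉₇₅ + z₀.₈₅)²(SD/δ)² = 2(1.960 + 1.036)²(0.7/0.2)² = 220 per group, not 200; 200 per group gives 81.5% power. That is a separate matter. Only the 0.2 and 0.7 are used below.

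**2. How often a covariate is selected.** Under random assignment the baseline p-value is uniform, so P(p < .20) = 0.20 and P(omitted) = 0.80. For three KAP scores, treated as independent, all three are omitted with probability 0.8³ = 0.51 and at least one with probability 1 − 0.2³ = 0.99. With 15 independent candidates (assumed number), 15 × 0.20 = 3 enter by chance.

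**3. Setting.** The group-by-setting table is 200, 200, 200, 200. Every expected count is also 200, so χ² = 0 and p = 1. The screen cannot select setting among the participants enrolled.

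**4. Operating characteristics, linear analysis of a continuous KAP score.** Let Z_B be the standardised baseline difference and E an independent standard normal variable.

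- Unadjusted: Z_U = θ + ρZ_B + √(1−ρ²)E.
- Adjusted for baseline: Z_A = θ/√(1−ρ²) + E.
- The rule uses Z_A if |Z_B| > 1.282 and Z_U otherwise.
- P(reject) = ∫ P(|Z_U| > 1.96 given Z_B = x) φ(x) dx over (−1.282, 1.282), plus 0.20 × P(|Z_A| > 1.96).
- θ = 0.2/(0.7√(2/n)), which is 2.857 at n = 200 and 4.041 at n = 400; θ = 0 for type I error.

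Worked case, ρ = 0.5, θ = 0: rejection is 0.0343 when baseline is omitted and 0.05 when it is included, so 0.8 × 0.0343 + 0.2 × 0.05 = 0.0374.

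| | ρ = 0.3 | ρ = 0.5 | ρ = 0.7 |
|---|---|---|---|
| Type I error, rule | 4.5% | 3.7% | 2.6% |
| Type I error, always adjust | 5.0% | 5.0% | 5.0% |
| Power at 400 per arm, rule | 98.5% | 98.9% | 99.5% |
| Power at 400 per arm, always adjust | 98.9% | 99.7% | >99.9% |
| Power at 200 per arm, rule | 82.7% | 84.8% | 87.8% |
| Power at 200 per arm, always adjust | 85.0% | 91.0% | 97.9% |

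In this calculation the type I error does not depend on n. Simulation at 200 per arm (20,000 trials per case) gave selection rates of 0.198 to 0.204 and type I error of 4.5%, 4.0% and 2.5%.

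The direction has a simple cause. Baseline is omitted only when it is nearly balanced, and then the unadjusted estimate varies less than its standard error claims.

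**5. Change scores.** Sample Size Justification speaks of a mean change. If change is analysed, with 0.7 kept as the SD of a single score, Z_U is replaced by (θ + (ρ−1)Z_B + √(1−ρ²)E)/√(2(1−ρ)). The same integral gives type I error of 3.3%, 3.7% and 4.2%, and power at 200 per arm of 72%, 85% and 97%. Subtracting baseline does not remove the problem.

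**The case against.** The strongest reply is that little is lost. The enrolled comparison has 400 per arm, where power is above 98% either way and the rule costs less than 1 point. That stands for the overall comparison of final scores. The larger loss applies at 200 per arm, the size within each setting and the size in Sample Size Justification.

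A second reply is that the named primary comparison is an unadjusted log-rank test, which the screen does not touch. This also stands: the figures describe adjusted linear models of a continuous score. They were not derived for the log-rank or Cox analysis.

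Third, the candidate confounders are not listed, and a condensed article may leave that list to a fuller document. Treating baseline KAP as a candidate is therefore an inference. If it is not one, this text gives it no route into the models at all.

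Fourth, if the study was truly quasi-experimental, the 80% and the error rates above do not follow. A significance screen would still be a weak way to choose confounders, since it ignores their relation to the outcome.

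Three stronger readings are tempting and not supported:

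- **More false positives.** A reader might infer this from error rates that differ from 5%. Every computed rate is below 5%.
- **Different covariates for different outcomes.** The screen looks only at groups and baseline variables, so on the same participants it returns one set for every outcome.
- **A trial known to be randomised with stratification by setting.** The article reports stratified counts and random assignment but does not say that randomisation was stratified, and it also uses the quasi-experimental label.

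**Conclusion.** The point holds as a modest fault in a stated rule. Given random assignment, each candidate is omitted from the adjusted models about 80% of the time regardless of prognostic value, and setting is always omitted. Neither result depends on ρ. The consequence is a conservative test (about 4.5%, 3.7% and 2.5% at assumed ρ of 0.3, 0.5 and 0.7, at either sample size) and lost precision. Against always adjusting, the power loss is under 1 point at 400 per arm and about 2 to 10 points at 200 per arm. These sizes assume a linear analysis of a continuous final score with difference 0.2 and SD 0.7. The change should be made, but the rule does not invalidate the overall comparison.

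**What to change.** 1. Delete both .20-level selection rules from Statistical Analysis.
2. State that each adjusted model includes the baseline value of the same outcome and urban/rural setting, whatever a baseline test shows. The proviso on baseline values is needed because Study Groups lists satisfaction with care only at follow-up.
3. Allow other covariates only if they are named before the follow-up data are analysed by group.
4. Reconcile the quasi-experimental label in the Abstract and Study Design with the random assignment in the Abstract and Study Groups, and state how allocation was actually done.

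The cost is wording. Baseline KAP and setting are already recorded, no new data are needed, and one analysis step is removed.
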